#### Data collection method

A case report form has been created for the study. For telephone follow-up a questionnaire has been created to record death or vascular events.

### Variables

It will be recorded the demographic baseline information of age, sex, marital status and employment status. Educational level and social class will also be recorded as potential confounding factors. Educational level will be grouped into three categories: high level (patients with university education), middle level (secondary education until age 16 -18) and low level (patients who haven't received any education or have only completed primary school). Social class will be measured by the Spanish National Occupation Classification. Drugs which may be related to cardiovascular diseases will be recorded (antiplatelet agents, warfarin, oral contraceptives, hormonal therapy, lipid lowering agents, antihypertensive and antidiabetic agents).

#### Co-morbidity study

Clinical history, date of diagnosis and treatment of hypertension, diabetes, atrial fibrillation, chronic obstructive pulmonary disease, renal disease and depression will be collected. The Charlson Comorbidity Index, which contains 19 comorbidity categories, will be calculated. Each index category has an associated weight, taken from the original Charlson's document [28], which is based on the adjusted mortality risk per year. The overall comorbidity score reflects the greater cumulative probability of mortality per year. The higher the score the more severe the comorbidity burden is. The Cumulative Illness Rating Scale (CIRS) will also be calculated. This index scores medical problems categorized into 14 organ systems from 0 to 4 points [29]. The general rules for the severity rating are the following: (0) no problem affecting this system or a problem of the past without clinical relevance, (1) current mild problem or severe problem of the past, (2) moderate disability or morbidity and/or requires a first-line therapy, (3) serious problem and/or significant disability and/or chronic conditions which are difficult to control (complex treatment regimen), (4) extremely serious problem and/or required immediate treatment and/or organ failure and/or severe functional impairment.

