## Background

In Spain, as in most Mediterranean countries, death rates from cardiovascular diseases have traditionally been lower compared with those in Anglo-Saxon and northern and central Europe [1]. However, they are still a priority public health problem because vascular diseases contribute to 30% of total mortality in developed countries, 56 million deaths worldwide, of which more than 125, 000 are in Spain [2]. The European guideline for vascular prevention [3] recommends that prevention strategies should include three main components: 1) a population strategy to try to change lifestyle, social, environmental and economic factors which are highly related to the disease occurrence 2) a secondary prevention strategy to reduce recurrences, complications rates and improve the disease prognostic and 3) a primary prevention strategy in high-risk population in which different interventions are more efficient than in general and low-risk population. In this last strategy, the key element is to identify these individuals through the use of risk functions. This strategy has some limitations at present, since sometimes the performance of such functions is insufficient, especially in patients classified as intermediate-risk (5-15% risk at 10 years) [4]. Several attempts to improve risk functions by using new risk factors markers have not increased their predictive ability, because of the autocorrelation of these emerging factors with classical risk ones [5,6]. With the available evidence we cannot assess the balance between risks and benefits of the studied factors for its widespread use in asymptomatic men and women with no history of coronary disease [7]. The general conclusion is that this issue is a priority in vascular prevention research.

There are three opportunity areas to improve the risk estimation in intermediate-risk population:

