### Objectives

To analyze whether the ABI and arterial stiffness measures (pulse wave velocity and cardio ankle vascular index) are associated independently with the incidence of vascular events and whether they can help to improve the predictive ability of risk equations based on traditional risk factors in intermediate-risk population.

To analyze whether the postprandial capillary glucose, glycated hemoglobin, and self-blood pressure measurement are associated independently with the incidence of vascular events and whether they can help to improve the predictive ability of risk equations based on classical risk factors in intermediate-risk population.

To analyze whether the presence of comorbidity measured by composite indices (Charlson Index, Cumulative Illness Rating score) is associated independently with the incidence of vascular events and whether they can help to improve the predictive ability of risk equations based on classical risk factors in intermediate-risk population.

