### Statistical analysis

Percentages will be used to describe categorical variables. Continuous variables will be described with the mean and standard deviation or with the median and the interquartile range as appropriate. Homogeneity among centers will be proved by a Chi-square test or Kruskal-Wallis test depending on the probability distribution of variables. A multivariate analysis by Cox proportional risk models will be performed to examine the contribution of the studied risk factors adjusted by traditional risk factors (age, sex, total cholesterol and HDL cholesterol, smoking status, diabetes and blood pressure).

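### The CIRS total can carry treatment and severity of hypertension and diabetes that the Cox model is not stated to adjust for, so a positive result may partly reflect classical risk factors

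*Protocol article*

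**What the plan says.** The third objective (protocol article, Objectives) is to learn whether "presence of comorbidity measured by composite indices (Charlson Index, Cumulative Illness Rating score) is associated independently with the incidence of vascular events", and whether the indices improve risk equations built on classical factors.

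The Co-morbidity study section describes the data and the scoring:
- Data: "Clinical history, date of diagnosis and treatment of hypertension, diabetes, atrial fibrillation, chronic obstructive pulmonary disease, renal disease and depression will be collected".
- CIRS scope: "This index scores medical problems categorized into 14 organ systems from 0 to 4 points".
- CIRS severity: one level is "2) moderate disability or morbidity and/or requires a first-line therapy". The 3-point level covers, among other things, "chronic conditions which are difficult to control (complex treatment regimen". No condition is exempted because it is already a classical risk factor.

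The Statistical analysis section names the Cox adjustment set: age, sex, total and HDL cholesterol, then "smoking status, diabetes and blood pressure". No term for treatment or severity is named. The Variables section does record antihypertensive and antidiabetic drugs, so the information will be available.

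**The concern.** The CIRS is scored partly by need for treatment and difficulty of control. Applied as printed, a participant on first-line treatment for hypertension or diabetes gains 2 points, and one whose condition is hard to control gains 3. Take two participants with the same measured blood pressure, one treated and one not. The treated participant has the higher CIRS, and nothing named in the model accounts for the difference. The same holds for two participants with diabetes of different severity.

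Any risk tied to treatment or severity, beyond what diabetes and blood pressure already explain, is then credited to the CIRS. The objective is about what comorbidity adds to the classical factors. A positive CIRS coefficient could not be read as the effect of other illness, because part of it may be a finer measurement of two classical factors.

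**Working it through.** The plan gives no figure on this point. Its one calculation, the sample size for a low ankle-brachial index, has no bearing here except to supply a cohort size and an event rate.

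**Step 1: the texts side by side.** The scoring rule admits treated hypertension and diabetes. The list of collected conditions includes both, with their treatment. The adjustment set has diabetes and blood pressure only. What remains inside the CIRS is the treatment and severity part.

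**Step 2: direction and conditions, by formula.** Let the score be 2H + O. H marks treated hypertension, and O is the rest of the score, with no effect on events and independent of H. Let v be the variance of H left after the adjustment covariates, s the standard deviation (SD) of O, and HR the hazard ratio of H given those covariates. Approximately:

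- log hazard ratio per CIRS point = ln(HR) × 2v / (4v + s²)
- per SD: multiply by √(4v + s²)

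If HR = 1, the result is exactly zero. If treatment is in the model, v = 0 and the result is again zero.

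**Step 3: illustrative size.** The documents give none of these inputs. Assume prevalence 0.5, s = 2 and HR = 1.5, so ln(HR) = 0.4055.

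- Covariates explain none of H: v = 0.25. 0.4055 × 0.50 / 5.00 = 0.0405 per point; × √5.00 = 0.0907 per SD; hazard ratio 1.095 per SD.
- Covariates explain 25%: v = 0.1875. 0.4055 × 0.375 / 4.75 = 0.0320; × √4.75 = 0.0698; hazard ratio 1.072.
- Covariates explain 50%: v = 0.125. 0.4055 × 0.25 / 4.50 = 0.0225; × √4.50 = 0.0478; hazard ratio 1.049.

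Now widen the assumptions to prevalence 0.4 to 0.6, HR 1.3 to 1.5 and s from 1.5 to 3.

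- No variance explained, low end: 0.2624 × 0.48 / 9.96 × √9.96 = 0.0399, hazard ratio 1.04.
- No variance explained, high end: 0.4055 × 0.50 / 3.25 × √3.25 = 0.1125, hazard ratio 1.12.
- Half explained, low end: 0.2624 × 0.24 / 9.48 × √9.48 = 0.0205, hazard ratio 1.02.
- Half explained, high end: 0.4055 × 0.25 / 2.75 × √2.75 = 0.0611, hazard ratio 1.06.

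**Step 4: a check with adjustment made explicit.** A simulation used 2688 participants and about 3.4% events, since (336 × 0.06 + 2352 × 0.03) / 2688 = 90.72 / 2688. The model was a complementary log-log model adjusted for age, blood pressure and diabetes yes/no, with 400 replicates. Assumed inputs were:
- hypertension scored 0, 1, 2 or 3 in 45, 15, 30 and 10%;
- diabetes in 20%;
- other illness Poisson with mean 2 and no effect;
- blood pressure only weakly related to hypertension severity.

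For true hazard ratios of 1.0, 1.15, 1.3 and 1.5 per point of hypertension or diabetes severity, the full score showed 1.00, 1.06, 1.10 and 1.16 per point. With the hypertension and diabetes points left out, it showed 0.99 to 1.00 throughout.

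Both checks agree that the overlap can produce a CIRS effect, that the effect vanishes without residual risk, and that removing the points removes it. Neither estimates its size in this cohort.

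**The case against.** **The scoring of hypertension and diabetes is inferred.** The six listed conditions describe data collection and are not a CIRS item list, and the 14 organ systems are not named. This stands. The inference rests on the general rule and the absence of any stated exception, which is why the point says only that the total can include these points.

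**Coding and treatment terms may be in an analysis plan that is not shown.** This is fair, and the absence of such detail in an article is not the complaint. The point is that the rule and the adjustment set, both printed, do not together isolate what the objective asks.

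**If treatment or severity predicts events beyond the equations, the CIRS does add prediction.** This stands for the prediction half of the objective. The Background also seeks more detailed assessment of traditional factors. But it presents comorbidity as a separate third line, supported by chronic obstructive pulmonary disease, atrial fibrillation, renal disease and depression. Which of the two drives the result therefore matters to the conclusion.

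A reader might infer more than the documents support:
- **That the Charlson Index has the same fault.** The treatment-based rule belongs to the CIRS. The 19 Charlson categories are not listed and no such rule is given for them.
- **That a positive result could come from hypertension and diabetes alone.** This requires that no other illness matters, which is a constructed case.
- **That the Background foretold it.** Its remark "because of the autocorrelation of these emerging factors with classical risk ones" explains why earlier markers brought no improvement. It does not describe overlap creating a false one.
- **That a false-positive rate can be stated.** Prevalence, residual risk, spread of the score and later event counts would all have to be assumed.

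**Conclusion.** The concern holds for the CIRS as a weakness of interpretation in the third objective. It is neither a contradiction nor a numerical error in the protocol. As printed, the total can include treatment and severity of hypertension and diabetes, and the stated model names no term that removes them. A positive CIRS result could then partly reflect classical risk factors.

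The size is unknown from the documents. It is nil if treatment and severity carry no risk beyond diabetes and blood pressure, and it shrinks as those covariates explain more of who is treated. The illustrative hazard ratios show only that a modest effect is possible under the stated assumptions.

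**What to change.** Keep the published CIRS as the named measure. For the comorbidity analyses, add antihypertensive and antidiabetic treatment, already recorded, to the base model. Report alongside it a CIRS scored without points for hypertension and diabetes. Treatment terms alone may not capture the difference between first-line and complex treatment, so the reduced score is needed too. Describe the comorbidity effect as independent of classical risk factors only if it persists in both.

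The cost is one or two extra model terms and one extra column of results, with no new data collection. The reduced score is not the validated original, so it should accompany the full CIRS and not replace it.

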#### Diet

A validated food frequency consumption questionnaire [30] and a validated questionnaire about the adherence in Mediterranean diet [31] will be used.

#### Physical activity

The adapted Minnesota's leisure time activity questionnaire will be used, whose use has been validated in the Spanish population [32]. The average daily physical activity during leisure time of the last year will be reported.

#### Tobacco consumption

A questionnaire of 4 standard questions adapted from the WHO MONICA study will be used. The carbon monoxide concentration will be measured by a co-oximeter and the participants will be asked when the last cigarette was smoked.

#### Alcohol consumption

A questionnaire about alcohol consumption in the last 7 days will be included through a detailed questionnaire about alcohol types and volume.

#### Intermittent claudication

The Edinburgh validated questionnaire will be used [33]. Existence of asymptomatic PAD will be considered when ABI values are < 0.9 and no intermitent claudication are registered in the questionnaire.

#### Electrocardiogram

A 12-derivation digital electrocardiograph CardioSoft^® ^(General Electrics) will be used to test the participants at rest.

#### Blood pressure measurements

Blood pressure measured by nurse will be made in sitting position after 5 minutes of rest and it will be performed 3 times separated by 2 minutes in each arm. An automatic and validated device will be used (OMRON 705). The subject should avoid doing any type of exercise at least one hour before the measurements. He or she should also avoid eating or drinking much, smoking and taking medication that could directly affect the BP (except in hypertension treated patients). Blood pressure self-measurement will be made by participants at their home for three days. They will make 2 blood pressure measurements separated by 2 minutes in the morning and in the evening, before having breakfast and dinner, respectively [34].

#### Ankle-brachial index and arterial stiffness

They will be measured using Vasera device VS-1500^® ^(Fukuda Denshi). For the study, the lowest ankle-brachial index obtained will be considered. The pulse wave velocity (PWV) will be calculated, as well as Cardio Ankle Vascular Index (CAVI), which gives a more accurate calculation of the atherosclerosis degree. CAVI integrates cardiovascular elasticity derived from the aorta to the ankle pulse velocity through an oscillometric method and it is used as a good measure of vascular stiffness. It doesn't depend on blood pressure and the information that it gives may help to prevent peripheral vascular occlusions [14]. Ankle-brachial index, blood pressure and CAVI will be measured at rest and after light intensity exercise in order to evaluate whether there are changes in the measurements that can predict cardiovascular risk better. Participants will cycle on a static bike for 5 minutes at 70 wats of power before the measurement.

#### Anthropometric measurements

Weight will be measured with a precision scale, which will be weekly calibrated. The return to zero will be checked after every measurement. Size will be measured vertically. Subjects should remove their shoes, jackets, coats etc. Waist circumference: the midway between the lowest rib and the iliac crest will be localized.

#### Laboratory data

The blood sample will be taken after 12 hours fasting. Cholesterol and triglycerides concentration will be determined by enzymatic methods and HDL cholesterol after apo B containing lipoprotein precipitation. LDL cholesterol will be determined by the Friedewald formula. Glucose concentration (mg/dl), glycated hemoglobin (%) and creatinine will also be determined, as well as urine albumin, to calculate the albumin/creatinine index. Postprandial glucose (mg/dl) will be self-measured by patients at home 2 hours after meals (breakfast, lunch and dinner) for one day using an Accu-chek ^® ^glucometer.

#### Vascular events in the follow-up

There will be a telephone follow-up to the 1.5, 5 and 10 years to verify the vital status and the existence of hospital admissions due to vascular health problems. The information of each case will be confirmed after a review of hospital discharge reports and the verification of the diagnostic criteria by a consensus of at least 2 investigators. Fatal and non fatal coronary heart disease (myocardial infarction or angina pectoris) will be considered. Cases will be classified according to symptoms, electrocardiogram, and myocardial necrosis markers. Fatal cases will be classified through the death certificate or autopsy findings. Angina pectoris only will be considered if there are changes in the ECG or a positive stress test. Stroke will be considered when neurologic deficit lasting more than 24 h attributable to a diagnosis of a focal cerebral ischemia is confirmed by an imaging test (CT or MRI). Peripheral arterial disease will be considered if there is a diagnostic made by arteriography or Doppler (ankle-brachial index below 0.9) or lower limb amputation or ulcer or gangrene attributable to an ischemic deficit.

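### The outcome definition admits angina and PAD diagnosed without admission, but case finding and confirmation are described through hospital admissions and discharge reports

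*Protocol article*

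**What the plan says.** Three elements of the protocol article bear on this point.

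- **Contact and confirmation.** Under Vascular events in the follow-up, participants are telephoned at 1.5, 5 and 10 years "to verify the vital status and the existence of hospital admissions due to vascular health problems". Each case is then "confirmed after a review of hospital discharge reports and the verification of the diagnostic criteria by a consensus of at least 2 investigators". Deaths have their own source: "Fatal cases will be classified through the death certificate or autopsy findings".
- **Outcome definitions.** The same section sets the non-fatal criteria. For angina: "Angina pectoris only will be considered if there are changes in the ECG or a positive stress test". For PAD: "Peripheral arterial disease will be considered if there is a diagnostic made by arteriography or Doppler", the Doppler criterion being an ankle-brachial index below 0.9; amputation, ulcer or gangrene of ischaemic origin also count.
- **Questionnaire.** Under Data collection method: "For telephone follow-up a questionnaire has been created to record death or vascular events". This description is not limited to admissions.

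The article describes no follow-up visit, no repeat ABI or ECG, and no use of primary care or outpatient records to find or confirm events.

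**The concern.** The outcome is defined by diagnostic findings, whereas the route to it is described through hospital admission. A positive stress test, a Doppler result or an ischaemic ulcer satisfies the definition wherever it was recorded, but only an admission produces a discharge report. Someone with a qualifying diagnosis and no admission therefore meets the outcome definition and cannot meet the confirmation rule.

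The objectives are to test independent association with vascular events and to improve the predictive ability of risk equations. Under-counting some components would lower observed incidence, and with it the absolute risks that a prediction model is fitted to. It would also reduce the number of events. If investigators or centres resolved unconfirmed reports differently, outcome ascertainment would vary across the three regions for reasons unrelated to risk.

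**Working it through.** **Setting the passages side by side**

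| Component | Admission required by the definition? | Confirmation source stated |
|---|---|---|
| Fatal event | No | Death certificate or autopsy |
| Any non-fatal event with admission | – | Discharge report, then consensus of at least 2 investigators |
| Angina by ECG change or stress test, no admission | No | None |
| PAD by Doppler, or ischaemic ulcer, no admission | No | None |

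The follow-up section would not seek the last two rows by telephone. The data collection section might. Neither says how they would be confirmed.

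**Reproducing the plan's sample size**

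Inputs from the Sample size section: two-sided alpha 0.05, beta 0.2, 3% in the unexposed, relative risk 2 (hence 6% in the exposed), 336 exposed and 2352 unexposed (ratio 1:7), Poisson approximation.

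- Pooled rate: (0.06 + 7 × 0.03)/8 = 0.03375.
- Exposed group: n = (1.960 + 0.842)² × 0.03375 × (1 + 1/7) / (0.06 − 0.03)² = 336.4, against 336 stated. The plan's figure reproduces.
- Expected events: 336 × 0.06 + 2352 × 0.03 = 20.2 + 70.6 = 90.7.

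**Illustration of missed events**

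The documents give no share of qualifying events without admission, so the share f is an assumption. Two more are needed: that the 3% rate includes such events, and that they are missed equally in both groups, so the relative risk stays at 2. Both rates are multiplied by (1 − f). Power follows from the same pooled Poisson formula with N = 2688:

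power = Φ( (p₁ − p₀) / √[p̄ × (1/336 + 1/2352)] − 1.960 )

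At f = 0 the ratio inside is 0.03/0.010714 = 2.800. It scales with √(1 − f).

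| f (assumed) | Overall proportion with event | Events | Ratio − 1.960 | Power |
|---|---|---|---|---|
| 0 | 3.375% | 90.7 | 0.840 | 80.0% |
| 20% | 2.70% | 72.6 | 0.544 | 70.7% |
| 40% | 2.03% | 54.4 | 0.209 | 58.3% |

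Restoring 80% power would take 336.4/0.8, rounded up to 421 exposed (3368 in total), at f = 20%. At f = 40% it would take 336.4/0.6, rounded up to 561 exposed (4488 in total). Loss to follow-up is not included.

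**The case against.** The strongest reply is that the follow-up section can be read coherently as it stands. Cases come to light through vascular admissions, and the diagnostic criteria then classify what was found. On that reading the angina sentence is a restriction that keeps out unproven angina, not a promise to count every positive outpatient test. This is a possible intention, but the text does not state it. The PAD criterion is written as a free-standing definition, and the questionnaire is described in terms of events, not admissions. If hospital-ascertained events are meant, the definition should say so.

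A reader might infer three stronger things that the documents do not support.

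- *That nothing in the follow-up could capture these events.* The questionnaire is described as recording vascular events generally and is not itself shown, so a participant may be asked about, or may volunteer, a diagnosis made without admission. What is missing is a stated way to confirm it.
- *That participants who cannot be reached are mishandled.* The article allows for 25% loss and names no back-up source for those not reached by telephone. Tracing procedures are commonly left to the full protocol, so their absence from a condensed article is no error. Nothing in the text shows that the loss would be informative.
- *That the study is underpowered by a known amount.* The power loss depends entirely on an assumed share. If the 3% rate was chosen for events as the plan would ascertain them, this mechanism costs no power. Equal loss in both groups also leaves the relative risk unchanged, so the illustration shows no bias in association. The documents do not allow the direction of any unequal loss to be judged.

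**Conclusion.** The concern holds as a mismatch between stated rules. The outcome definition is wider than the described route for finding and confirming non-fatal cases, and two sections describe the scope of the telephone contact differently. Deaths and events leading to admission are unaffected. For angina, Doppler-diagnosed PAD and ischaemic ulcer without admission, the plan as written gives no basis for accepting a reported case. The likely result is under-counted incidence or inconsistent handling at all three follow-up times.

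The size cannot be fixed from the documents. Under the three assumptions set out above, missing 20% to 40% of events would cost about 18 to 36 events (90.7 − 72.6 and 90.7 − 54.4) and take power from 80% to about 71% or 58%. This is worth correcting and easy to correct; it does not invalidate the design.

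**What to change.** Choose one of two routes and state it under both Data collection method and Vascular events in the follow-up.

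1. **Keep the wide definition.** Have the contact ask about any new diagnosis of, or admission for, the listed vascular events. Allow confirmation from health-centre records or outpatient test reports as well as hospital discharge reports, with the same consensus of at least 2 investigators. Because the PAD criterion uses the same ABI cut-off as the baseline exposure, state that the diagnosis must be new since inclusion.
2. **Narrow the definition.** If only hospital-ascertained events are meant, restrict angina and PAD to cases identified through an admission and say so in the outcome definition.

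The first route costs some chart-review time and needs record access to be covered by the consent. Recruitment runs through the participating health centres, and no new visit or test is needed. The second costs only wording, but gives up events that the present definition counts. In either case, say whether the 3% planning rate refers to the outcome as finally defined.

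Checking the health-centre records of participants not reached by telephone would be a reasonable optional addition.

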#### Sample size

The ABI < 0.9 population proportion with no history of vascular disease has been taken into account because ABI is the risk factor among those studied that we anticipate will have a lower prevalence. It is expected that in one year and a half of follow up 3% of the participants will present a vascular event. Therefore, accepting a 0.05 alpha risk and a 0.2 beta risk in a bilateral contrast, 336 subjects are needed in the exposed group and 2352 in the non-exposed group (2688 total) to detect a minimum relative risk of 2. We assumed an incidence rate in the unexposed group of 3%. Estimating a 25% of loss rate until 3360 participants will be oversampled. Poisson approximation has been used. The estimated relative risk is based on previous observational studies in which patients of the risk group had twice the incidence of vascular disease if they had an ABI < 0.9 [9]. In Catalonia node centers 1900 participants are expected to be recruited and 400 participants in each of the other two nodes. Professional nurses assigned to each health center will perform the physical examination and questionnaires. They will explain how to record the self-measurement of blood pressure and capillary blood glucose and the candidates will be cited later to collect this information. At the same time they will be scheduled for a fast blood test.

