### Ethical considerations

The study has received ethical approval from the Research Ethics Committee of the Institut d'Investigació en Atenció Primària Jordi Gol (Primary Care Research Institute Jordi Gol). Participants will be informed about the examinations performed, they will receive an information document and they will be asked for the informed consent prior to their inclusion. The principles of human experimentation, as the Helsinki Agreement, will be respected. Access to the information obtained from any analysis will be guaranteed. Confidentiality rules will be respected and the participants will be informed about the 5^th ^Article of the15/1999 Spanish organic Law, about the regulation of the automatic processing of personal data (personal data may be automatically processed and the participants have the rights to consult, modify or delete their personal data file).

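### Test-dependent angina and PAD count as full events while marker results are not concealed, so extra testing could inflate associations; a secondary analysis on harder events would show how far

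*Protocol article*

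**What the plan says.** All references are to the protocol article.

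- **Event definition (Vascular events in the follow-up).** Fatal and non-fatal coronary disease, stroke and PAD all count. On angina: "Angina pectoris only will be considered if there are changes in the ECG or a positive stress test". On PAD: "Peripheral arterial disease will be considered if there is a diagnostic made by arteriography or Doppler". PAD also counts through amputation, ulcer or gangrene of ischaemic cause. Stroke needs imaging confirmation, and fatal cases are classified from the death certificate or autopsy.
- **Case finding (same section).** Telephone follow-up asks about vital status and admissions for vascular problems. Each case is confirmed from hospital discharge reports and by consensus of at least two investigators. Whether they are masked to the baseline markers is not stated.
- **Who sees the markers.** Under Sample size: "Professional nurses assigned to each health center will perform the physical examination and questionnaires". Under Blood pressure measurements and Laboratory data, participants take their own home pressure and postprandial glucose readings. Under Ethical considerations: "Access to the information obtained from any analysis will be guaranteed". No recipient is named there, and nothing says that results are withheld from participants or clinicians.
- **Analysis (Statistical analysis).** Cox models adjust each marker for age, sex, total and HDL cholesterol, smoking, diabetes and blood pressure.

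**The concern.** Infarction, stroke and coronary death usually come to light however closely a person is watched. Angina confirmed by stress test, and PAD confirmed by arteriography or Doppler, are counted only if someone orders the test. If people with an abnormal ABI, stiffness index, home pressure or glucose are investigated more readily, they accumulate more counted events even when their underlying risk is no higher. Adjustment for baseline traditional factors cannot remove differences in testing that arise later.

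The error would push a marker with no prognostic value above a relative risk of 1, which is the direction that produces a false new risk factor. The Objectives ask exactly whether these markers are independently associated with incidence.

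This is a different issue from ABI below 0.9 serving both as the exposure and as a Doppler criterion for PAD. It also reaches angina, arteriography and the other markers, and would survive a repair of the PAD definition.

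**Working it through.** **1. The plan's own figure.** Inputs from Sample size: "accepting a 0.05 alpha risk and a 0.2 beta risk in a bilateral contrast"; "We assumed an incidence rate in the unexposed group of 3" per cent; "to detect a minimum relative risk of 2"; and "336 subjects are needed in the exposed group and 2352 in the non-exposed group (2688 total", a ratio of 1:7. Poisson approximation with the null variance in both terms:

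n(exposed) = (1.960 + 0.842)² × r̄ × (1 + 1/7) / (0.06 − 0.03)², with r̄ = (0.06 + 7 × 0.03)/8 = 0.03375.

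This gives 7.849 × 0.03375 × 1.1429 / 0.0009 = 336.4, so the stated 336 reproduces. The group sizes and the 3% rate can be used below.

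**2. Apparent relative risk of a null marker.** The article gives neither the share of events that depend on testing (s) nor the ratio of detection in exposed to unexposed people (k). Both are assumed: s = 30%, 50%, 70%; k = 1.25, 1.5, 2. With a true RR of 1:

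apparent RR = (1 − s) + s × k.

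**3. Chance of a significant ABI result (two-sided 5%).**

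SE = √[1/(336 × 0.03 × RR) + 1/(2352 × 0.03)], z = ln(RR)/SE, chance = Φ(z − 1.96) + Φ(−z − 1.96).

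Example, s = 50% and k = 2: RR = 0.5 + 0.5 × 2 = 1.50. Expected events are 15.12 and 70.56, SE = 0.283, z = 0.405/0.283 = 1.43, chance = 0.299.

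| s | k = 1.25 | k = 1.5 | k = 2 |
|---|---|---|---|
| 30% | RR 1.075, 5.6% | RR 1.15, 7.3% | RR 1.30, 14% |
| 50% | RR 1.125, 6.6% | RR 1.25, 11% | RR 1.50, 30% |
| 70% | RR 1.175, 8.1% | RR 1.35, 17% | RR 1.70, 50% |

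At k = 1.25 the error rate barely moves from 5%. It becomes material only when both the share and the detection ratio are sizeable.

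**4. Why these are upper bounds for a given s and k.** The formula turns k times as many work-ups into k times as many counted events. It assumes that the extra work-ups yield confirmed events at the same rate as ordinary ones. Marker-driven tests would probably have a lower yield, and some would involve no admission.

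**5. Power of an analysis without test-dependent events.** True RR 2, same formula. All events: 20.16 exposed and 70.56 unexposed, SE = 0.2525, z = 0.693/0.2525 = 2.745, power 78%. (It is not exactly 80% because this log-rate formula differs from the one in step 1.) Multiplying both event counts by 1 − s:

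| Events removed | Exposed / unexposed events | Power |
|---|---|---|
| none | 20.2 / 70.6 | 78% |
| 30% | 14.1 / 49.4 | 63% |
| 50% | 10.1 / 35.3 | 49% |
| 70% | 6.0 / 21.2 | 32% |

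**The case against.** The causal link is not in the text. A reader might infer that an abnormal marker does prompt stress tests or arteriography, and that ABI, pulse wave velocity and CAVI results are known to the treating clinician. The article says neither. The access statement names no recipient, and a nurse taking a measurement is not the same as a clinician acting on it. Only the home readings are plainly known to participants. This part of the objection stands, so the point can be put only as a possibility.

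The event definition also has safeguards. Cases are sought through hospital admissions and confirmed from discharge reports by at least two investigators, and the angina sentence is itself a restriction that demands objective evidence. An outpatient test ordered because of a marker is not in itself an admission. This narrows the route but does not close it. Confirmation shows that the disease is real, not that it would have been found equally often in unexposed people, and an admission for investigation would pass every step.

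It would be wrong to say that PAD is found only through tests, since amputation, ulcer and gangrene count as well.

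Finally, component or hard-event analyses may already sit in a full protocol or analysis plan that is not shown. Their absence from a condensed article is therefore no fault. What remains is the event definition, which the article does fix.

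**Conclusion.** The point holds as a possible detection bias, not a demonstrated one. The composite gives full weight to angina and PAD diagnoses that depend on a test being ordered, the markers are not concealed, and the stated Cox adjustment cannot remove differences in later testing.

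The documents cannot fix the size. Under the assumed ranges the bias runs from negligible (RR about 1.08, about 6% significant results) to serious (RR 1.70, about 50%), as an upper bound in each case. A reader might conclude that any positive finding would be an artefact of disclosure; the documents do not support that. This is a worthwhile, inexpensive improvement rather than a defect that invalidates the design.

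**What to change.** In Vascular events in the follow-up and Statistical analysis:

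- Pre-specify, for every marker, a secondary analysis restricted to events that depend little on elective testing: myocardial infarction, imaging-confirmed ischaemic stroke, coronary death, and amputation, ulcer or gangrene of ischaemic cause.
- Report angina and test-diagnosed PAD separately.
- State that a claim of independent association will be qualified if it rests only on those two components.
- Judge consistency on estimates and confidence intervals. Do not require an association of similar size in the restricted analysis: a genuine marker may relate more strongly to PAD or angina than to infarction or stroke, and such a rule could reject it.

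Cases are already classified by type, so this should need wording only and no new data. The downside is fewer events and lower power: at RR 2, about 63%, 49% or 32% if 30%, 50% or 70% of events are removed, against 78% with all events. The restricted analysis should therefore be secondary, and a non-significant result in it should not be read as evidence against a marker.
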